#### Acceptability of the intervention and barriers to participation

It is important to explore barriers to participation during feasibility work because unforeseen challenges of recruitment can lead to early termination of definitive trials [27]. Attendance and exercise logbooks will be used to monitor non-adherence. The instructor will communicate with non-adherent participants to understand the reasons and barriers for non-adherence and to develop appropriate strategies to improve adherence (e.g., scheduling another time of day for performing home exercises, or reverting to the Tai Chi moves from the last week if the new move is too challenging, etc.). In addition to monitoring adherence, exercise class sessions will be randomly audio-recorded. The principal researcher will listen to the audio-recordings and document absence or presence of core parts of the intervention to check intervention fidelity.

Furthermore, to assess the acceptability of the intervention, each participant in the intervention group will be invited to participate in face-to-face or video call semi-structured interviews based on participants’ preferences within 1 month after the final follow-up. Visual materials such as video or photos of the exercise will be shown to the participants at the beginning of the interview to help them recall the content of the intervention program. The interviews aim to deepen our understanding of the barriers and facilitators to their participation in the intervention, and ways to improve adherence. All interviews will be audio-recorded after obtaining informed consent.

#### Sample size estimation for the future definitive trial

While the current feasibility trial is not powered to determine the efficacy of interventions, its findings will help estimate the standard deviation (SD) of the primary outcome (The Chinese version of Knee Injury and Osteoarthritis Outcome Scale (KOOS)) so as to inform the sample size calculation for the effectiveness trial. There are no plans to conduct interim analyses, i.e., while participant recruitment is on-going or before the final assessments are completed.

### Secondary endpoints

During the baseline assessments (1 week before TKA or baseline), participants will provide their demographic information and complete a set of questionnaires with the help of a research assistant if required (Table 1). The same set of questionnaires and assessment procedures will be repeated at the 6-, 12-, 24-, and 52-week post-TKA follow-ups in the TKA groups, and at the 12 and 52 weeks from baseline for the untreated asymptomatic controls.

**Table 1 Tab1:** Outcome measures of secondary endpoints at different time points for participants

Types of measure	Assessments	Measurement time				
		Pre-op (Baseline)	Postop 6 wk	Postop 12 wk	Postop 24 wk	Postop 52 wk
**Subjective assessments**						
Sociodemographic characteristics	Age, sex, weight, height, dominant leg, marital status, number of people in the household, smoking habit, educational level, work status (number of working hours per week), occupation, alcohol/smoking status, history of trips/ falls, elevator landing or non-elevator landing flat	x				
Comorbidities	List of diseases: respiratory disease, hypertension, cardiovascular disease, eye problems, hallux valgus, previous hip or knee arthroplasty	x				
Pain	11-point numeric pain rating scale [28]	x	x	x	x	x
Physical function	Chinese version of Knee Injury and Osteoarthritis Outcome Score [29]	x	x	x	x	x
Depression	Chinese version geriatric depression scale [30]	x	x	x	x	x
Physical activity	Physical Activity Scale for the Elderly (Chinese version) [31]	x	x	x	x	x
Global impression of change in the intervention/ usual care	Self-perceived global changes				x	x
Fear of falling	Falls Efficacy Scale [32]	x	x	x	x	x
**Physical assessments**						
Range of motion	Lower limb joint range of motion by goniometer	x	x	x	x	x
Balance	Brief-Balance Evaluation System test [33]	x	x	x	x	x
Static and dynamic stability	Functional tests using two wearable inertial sensors during tandem stance, a timed up-and-go test, and a 6-min walk test.	x	x	x	x	x
Physical activity over 3 days	Activity monitoring for 3 days in a week	x		x	x	x

Note: The asymptomatic controls will only undergo follow-ups at 12-week and 52-week after the baseline

*TKA* total knee arthroplasty, *mth* month, *post-op* post-operation, *pre-op* pre-operation, *wk* = week

### Primary outcomes for a future definitive trial (Table 1)

#### Self-reported physical function

The Chinese version of Knee Injury and Osteoarthritis Outcome Scale (KOOS) will be used to document self-reported physical function and to evaluate knee status before/after TKA [29].

#### Number of trips/falls

The number of trips, falls, and fall-related injuries in the 12 months before baseline will be documented. During the follow-up, trips/ falls will be recorded using a trip/fall diary.

### Secondary outcomes for a future definitive trial (Table 1)

#### Objective measures of static and dynamic stability

Three small wireless and wearable inertial motion sensors (OPAL, APDM Inc., Portland, USA; sampling frequency of 128 Hz) will be used to assess the static and dynamic balance of participants during functional tasks. When wearing the sensors, participants will perform a tandem stance test with eyes open and eyes closed, the TUG and the 6MWT. This method has been found to be useful in characterizing gait stability of people with and without Parkinson’s disease [27, 34] and discriminating older fallers from non-fallers [35].

#### Knee pain

The NPRS is a gold standard for pain measurement [36, 37] given its high reliability, sensitivity and validity [28].

#### Depressive symptoms

Depressive symptoms will be examined by the short form Chinese version of the Geriatric Depression Scale (GDS), which comprises 15 questions [30].

#### Physical activity levels

Physical activity will be assessed by the Physical Activity Scale for the Elderly (Chinese version), which is a 12-item questionnaire that documents leisure, physical, household, and work-related activities over the last 7 days [31].

#### Fear of falling

Concern of falling will be measured with the Falls Efficacy Scale (FESI) [32], which showed good reliability and validity in measuring fear of falling in frail older people [38].

#### Global impression of change

Symptom severity, treatment response and the efficacy of treatment 24 weeks post-TKA will be measured by the Global Impression of change scale.

#### Joint range of motion

The ranges of motion of hip, knee, and ankle joints will be evaluated using a goniometer. These assessments are chosen because limited knee/ankle joint ranges have been reported as potential risk factors for falls [5].

#### Balance assessment

The Brief-Balance Evaluation Systems test comprises six static and six dynamic tasks of different difficulty levels [33].

#### Remote monitoring of physical activity

To quantify physical activity levels under free-living conditions, each TKA participant will wear an activity monitor to track physical activity over 72 h (from Thursday night to Sunday night) at 1 week before TKA, and again for another 3 days during the 12th, 24th, and 52nd weeks after TKA. Similarly, asymptomatic controls will undergo physical activity monitoring using the sensor for a 72-h period week following baseline, and during 12th and 52nd weeks of follow-up.

## Statistical analysis

The data regarding the feasibility, acceptability, adverse events, intervention adherence, missing data rates and data completion rates will be summarized using descriptive statistics. The experience and perception of participants toward the RCT solicited from semi-structured interviews will be analyzed by framework analysis [39, 40].

To determine the feasibility of studying the proposed outcomes in a definitive trial, inferential analysis will be conducted at 95% confidence intervals, and the significance level will be set at 0.05. The effect size of each intervention outcome will also be estimated. Descriptive statistics will be used to summarize patient demographic data. Baseline demographic and clinical variables (such as BMI, medication, number of comorbidities) in the three groups will be compared using analyses of variance (ANOVAs) and Kruskal-Wallis tests for parametric and nonparametric data, respectively. Any baseline variables that show significant between-group differences will be used as covariates in subsequent between-group analyses of outcome measures. Separate two-way repeated measures analyses of covariate (ANCOVA) or ANOVA will be used to evaluate within- and between-group changes in various outcome measures at several follow-up time points (i.e., 6, 12, 24, and 52 weeks after TKA for TKA patients, and 12 and 24 weeks after baseline for asymptomatic controls) in the three groups. Statistical analyses will be conducted using SPSS version 21.0 (IBM Corporation, NY, USA). Following the intention-to-treat principle, between-group differences in primary and secondary continuous outcomes in all randomized participants at different time points will be analyzed. Per-protocol analysis will also be reported for all planned outcomes in participants who strictly followed the protocol.

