**Methods:**

A single-blinded 2-arm pilot randomized controlled trial will recruit 52 community-dwelling post-TKA patients (aged > 60 years) in Hong Kong. In addition, 26 untreated asymptomatic controls will be recruited for comparison purposes. The TKA patients will be randomized into either a 12-week multimodal Tai Chi rehabilitation group or a postoperative usual care group (26 each). Participants will perform the outcome assessments at baseline, 6, 12, 24, and 52 weeks after TKA, while asymptomatic controls will have the same assessments at baseline, 12, and 52 weeks after baseline. The rate of recruitment, retention, and attrition, as well as adherence to the intervention, will be measured and used to determine the feasibility of the study and whether a full-scale effectiveness trial is warranted. Further, qualitative interviews will be conducted to explore the acceptability and possible barriers to the implementation of the intervention. Primary and secondary outcomes including both patient-reported surveys and performance-based tests will be compared within and between groups.

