### Sample size

No formal sample size calculation was performed for this feasibility study. However, a minimum sample size for a pilot study to evaluate the feasibility of conducting a full-scale trial is suggested to be 50 per study [18, 19]. A total of 78 patients (26 per arm) were deemed an appropriate sample size for this trial to estimate the recruitment and retention rates and explore the acceptability of the intervention.

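### Significance tests at the 0.05 level are given as the way to determine whether the outcomes are feasible to study, a question that a P value does not answer, in a trial declared not powered for efficacy

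*Protocol article*

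**What the plan says.** The protocol article deals with this in four places.

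- **Statistical analysis.** The section first plans descriptive summaries of feasibility, acceptability, adherence, missing data and completion. It then turns to the outcomes: "To determine the feasibility of studying the proposed outcomes in a definitive trial, inferential analysis will be conducted at 95% confidence intervals". The threshold for these tests is 0.05. It also plans an effect size for each outcome, and between-group comparisons of the primary and secondary continuous outcomes at several time points, by intention to treat and per protocol.
- **Sample size.** "No formal sample size calculation was performed for this feasibility study". The size rests on a rule of thumb for pilots that "is suggested to be 50 per study".
- **Sample size estimation for the future definitive trial.** The article says that "the current feasibility trial is not powered to determine the efficacy of interventions", and that the pilot will supply an SD for KOOS.
- **Primary endpoint.** The feasibility work is meant to inform which primary outcome the full trial uses, and to give an attrition rate for its sample size.

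**The concern.** The sentence names a purpose, the feasibility of studying the outcomes, and a method, inferential analysis with a 0.05 level. The method does not serve the purpose. An outcome is feasible if participants can complete it, if little of it is missing, and if its SD is small enough for a realistic definitive trial. A P value for the arm difference mixes the true effect, the SD and the sample size, and the article itself says that this sample size was not chosen to detect an effect.

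The choice of the definitive primary outcome is at stake. The article lists two candidates, KOOS and trips/falls, and a further set of secondary outcomes. If significance is taken as a sign of feasibility, a sound and responsive outcome can look unsuitable because the pilot is small, and an outcome with no effect can look promising by chance.

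**Working it through.** **The plan's own figure.** 26 × 3 = 78 in total and 26 × 2 = 52 randomized, which meets the cited minimum of 50 per study. The figure reproduces. There is no power calculation to reproduce, because the article gives no effect size, SD or power.

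**Inputs.**
- From the article: 26 per arm, significance level 0.05, and 11 outcome headings under the primary and secondary outcomes for a future definitive trial.
- Assumed: a two-sided test (the article does not say, but pairs the level with 95% intervals); true differences d of 0.2 to 0.8 SD; attrition of 0% or about 20% (21 per arm); correlation r of 0.5 to 0.7 with an earlier score.

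**1. Power of one unadjusted comparison at one visit.** The noncentrality is d × √(n/2), on 2n − 2 degrees of freedom. For d = 0.5 and n = 26 it is 0.5 × √13 = 1.80, against a critical t of 2.01 on 50 degrees of freedom.

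| True difference (SD) | Power, 26 per arm | Power, 21 per arm |
|---|---|---|
| 0.2 | 11% | 10% |
| 0.3 | 19% | 16% |
| 0.5 | 42% | 35% |
| 0.8 | 81% | 72% |

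With 26 per arm, power reaches 80% only at d = 0.79. By the normal approximation, 80% power at d = 0.5 needs 63 per arm.

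**2. The same with adjustment for an earlier score.** The effective difference is d/√(1 − r²).
- r = 0.5: 0.5/√0.75 = 0.577 SD. Power is 53% with 26 per arm and 45% with 21.
- r = 0.7: 0.5/√0.51 = 0.700 SD. Power is 70% with 26 per arm and 60% with 21.

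**3. Chance of at least one false positive at one visit.** If k outcomes have no true effect and are independent, the chance is 1 − 0.95^k.
- k = 11: 1 − 0.95¹¹ = 0.43.
- k = 12: 1 − 0.95¹² = 0.46.

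The k = 12 case allows for a heading that holds more than one measure. The outcomes are related, so these figures are an upper guide for one visit. By simulation, 12 outcomes with a common pairwise correlation of 0.3 give about 40%, and with 0.7 about 23% (both correlations assumed). Further visits and the per-protocol analyses add more chances, which are not computed here.

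**4. What estimation gives instead.** The half-width of the 95% interval for a difference is 2.01 × √(2/26) = 0.56 SD. For the SD itself, on 50 degrees of freedom, the 95% limits are √(50/χ²) at the two tails, or 0.84 to 1.24 times the estimate. Both show openly how little or how much the pilot has learned.

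**The case against.** The strongest reply is that the sentence is loose drafting and little depends on it. The section also plans confidence intervals and effect sizes, and it reports missing-data and completion rates descriptively. The article is open about the lack of power. The sample-size inputs it names for the full trial are the SD and the attrition rate, not the observed effect. All of this stands. It limits the point to the role given to the 0.05 level, and it means that most of what should replace that level is already planned.

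The power figures can also be challenged. They come from a simple t-test, whereas the plan uses repeated-measures ANOVA or ANCOVA, and 0.5 SD is an assumed effect. At 0.8 SD even the simple test has 81% power. This also stands, which is why the adjusted range is shown. The argument does not depend on one effect size: even a well-powered test would not show whether an outcome can be collected.

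A reader might go further and infer that the decision to proceed rests on P values. The text does not support that. The Abstract says that recruitment, retention, attrition and adherence will be "used to determine the feasibility of the study and whether a full-scale effectiveness trial is warranted". The Background gives preliminary data a similar role but names no test, and nowhere does the article say that an outcome is kept or dropped by its P value. A reader might also object that no progression thresholds are printed for those rates. A condensed article may leave them to the full protocol or analysis plan, which are not shown, so their absence here is not a finding.

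**Conclusion.** The point holds in a narrow form. The article makes inferential analysis at the 0.05 level the means of determining outcome feasibility. That does not answer the question, and it sits badly beside the article's own statement on power. If a reader of the results used significance to help choose the primary outcome, the choice would be unreliable in both directions. A true 0.5 SD effect would be missed more often than not without adjustment (power about 42%), and in about 30% to 47% of cases with it (power about 53% to 70%). At one visit, some null outcome would reach significance with a probability of up to 43% to 46%, or about 23% to 40% at the correlations assumed above. These figures rest on the assumed effect size, on a two-sided test, on no attrition and on one visit. The total of 78 is not in question.

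**What to change.** In Statistical analysis, reword the sentence so that the 0.05 level is no longer the basis for outcome feasibility. It could say that:

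- between-arm differences and SDs will be reported with 95% confidence intervals, as planning estimates only;
- the feasibility of each outcome will be judged from its completion and missing-data rates, which the plan already collects.

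This agrees with the article's stated aim of estimating the KOOS SD and the attrition rate for the definitive trial. It needs no added participants, visits or measurements. The cost is that the pilot gives up reporting any efficacy comparison as statistically significant.

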### Recruitment

Participants scheduled for TKA will be recruited from the osteoarthritis clinics of two hospitals in Hong Kong. It is anticipated that at least 10 TKA patients will be eligible for this study every month and the recruitment will take place over a 2-year period. A trained researcher will contact potential participants who are scheduled for TKA by phone to provide the required information regarding the current study (including objectives, eligibility criteria, and interventions). Those interested will be scheduled for an in-person visit to a physiotherapy department at one of the participating hospitals. A physiotherapist/trained research assistant will check the eligibility of the participant and assess cognitive function with the Mini-Mental State Examination [17], if this assessment has not been recently administered. After obtaining written consent, participants will undergo baseline assessments on the same day. Untreated asymptomatic controls will be recruited from community centers through posters and will undergo the same baseline assessments after obtaining informed consent by blinded physiotherapists/a trained research assistant at one of the two participating hospitals. The reasons for exclusion and for non-participation of eligible candidates will be documented in a screening log.

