### Inclusion and exclusion criteria of participants

TKA participants will be eligible for this study if they are (1) aged 60 years or above, (2) planning to undergo primary TKA within 1 month, and (3) living independently in the community. People will be excluded if they are living in assisted living facilities, requiring nursing care, or planning to reside away from the hospital district within 1 year, or they have prior experience in practicing Tai Chi exercise for at least 3 months. Other exclusion criteria include the following: unstable medical conditions, fracture of lower limbs, malignancy in the last 5 years, lower limb prosthesis/amputation, congenital defect that is considered to cause the present complaint, systemic inflammatory and autoimmune diseases, previous osteotomy, neurological diseases (e.g., Parkinson’s disease, stroke), blindness, revision TKA, complications after primary TKA, and cognitive impairment as indicated by a Mini-Mental State Examination score < 19 [17]. Untreated asymptomatic controls will include a non-randomized cohort recruited using the same selection criteria with the exceptions that they must report no knee pain in the last 3 years, or have no history of TKA or total hip arthroplasty.

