### Randomization and allocation

Upon completion of the 12-week post-operation assessments, TKA participants will be randomized into either the intervention or the usual care group. Permuted blocks using a computer-generated random number schedule will be used to determine the randomization order. Group assignment will be concealed in sealed sequentially numbered opaque envelopes and administered by a research assistant at The Hong Kong Polytechnic University not involved in the study. In addition, various methods will be employed to keep participant data confidential and secure including using password-protected files, limiting access to only those on the study team who require identifiable data, and using de-identified data when possible.

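### Covariates are picked by baseline significance tests across three groups, one of them not randomised, so adjustment follows patient-versus-control differences and chance, not prognosis

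*Protocol article*

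**What the plan says.** All of the analysis wording is in the protocol article, Statistical analysis. The section opens the candidate list with "Baseline demographic and clinical variables (such as BMI, medication, number of comorbidities", so the list is illustrative and not closed. It says that these variables "in the three groups will be compared using analyses of variance (ANOVAs) and Kruskal-Wallis tests for parametric and nonparametric data, respectively". On the threshold it says "the significance level will be set at 0.05". The selection rule follows: "Any baseline variables that show significant between-group differences will be used as covariates in subsequent between-group analyses of outcome measures". The outcome models are repeated-measures ANCOVA or ANOVA in the three groups. An intention-to-treat comparison of the randomised participants is also planned, but no separate covariate rule is given for it.

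Only two of the three groups are randomised. Randomization and allocation says "TKA participants will be randomized into either the intervention or the usual care group", and this happens after the 12-week post-operative assessment. The third group differs by design. Inclusion and exclusion criteria says "Untreated asymptomatic controls will include a non-randomized cohort recruited using the same selection criteria with the exceptions that they must report no knee pain", and Recruitment says "Untreated asymptomatic controls will be recruited from community centers through posters", whereas the TKA patients come from hospital osteoarthritis clinics. Under Secondary endpoints, baseline for TKA patients is one week before surgery.

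**The concern.** A baseline difference between two randomised arms is due to chance, so its P value is no guide to whether adjustment is worthwhile. What matters is how strongly the variable predicts the outcome, and the rule never asks this.

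The omnibus test also mixes two different contrasts. One is between the randomised arms, where no systematic difference exists. The other is between surgical patients and people chosen for having no knee pain, where differences are expected for some variables. A variable can enter the randomised comparison only because controls differ from patients.

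Four things are at stake:
- The adjusted model is fixed only after the data are seen.
- Precision may be lost where there are only 26 patients per arm.
- The most natural covariate for the randomised comparison, the same outcome measured at week 12 just before randomisation, is never fixed as one.
- If pre-operative pain or function is among the tested variables, adjusting for it would remove part of the gap to asymptomatic controls, which is what the third group was recruited to describe.

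**Working it through.** **Inputs from the protocol.** There are 26 per group and three groups (Sample size: 3 × 26 = 78, of whom 2 × 26 = 52 are randomised), and the level is 0.05 (Statistical analysis). The article makes no power calculation and states no figure for this rule, so there is nothing to reproduce.

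**Inputs assumed.** The protocol does not give the shift of controls from patients, the correlation of a covariate with outcome, or the number of variables tested. Ranges are shown.

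**1. How often a variable is selected when the TKA arms are identical.** A one-way ANOVA on three groups of 26 has 2 and 75 degrees of freedom and a 5% critical value of 3.119. With group means (0, 0, D) in SD units, the noncentrality is 26 × (2/3) × D² = 17.33 D². The selection probability is the upper tail of the noncentral F distribution.

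| Control shift D (SD) | Noncentrality | P(selected) |
|---|---|---|
| 0 | 0 | 0.05 |
| 0.2 | 0.69 | 0.10 |
| 0.3 | 1.56 | 0.18 |
| 0.5 | 4.33 | 0.43 |
| 0.8 | 11.09 | 0.84 |
| 1.0 | 17.33 | 0.96 |

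**2. How often a real imbalance between the TKA arms is caught.** With means (0, 0.5, 0.25), so that the arms are 0.5 SD apart and controls midway, the noncentrality is 26 × 0.5² / 2 = 3.25 and P(selected) = 0.33.

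**3. Whether prognosis plays a part.** Two randomised arms plus controls were simulated with one covariate and one follow-up outcome, 40,000 runs per setting. The covariate is selected about 5% of the time with no control shift and about 84% of the time with a 0.8 SD shift, whether its correlation with outcome is 0 or 0.7.

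**4. Precision of the two-arm estimate** in the same simulation (SD of the estimate, in outcome SD units):

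| Correlation r | Control shift | Unadjusted | Planned rule | Covariate prespecified |
|---|---|---|---|---|
| 0.5 | 0 | 0.276 | 0.269 | 0.242 |
| 0.7 | 0 | 0.276 | 0.263 | 0.200 |
| 0.5 | 0.8 | 0.275 | 0.245 | 0.241 |
| 0.7 | 0.8 | 0.278 | 0.209 | 0.201 |

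With no shift, the rule forgoes most of the available gain. When the shift happens to bring in a prognostic variable, the loss is small.

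**5. What a fixed week-12 covariate would give.** Assume a correlation r between week 12 and follow-up and equal variances at the two times. Relative to the variance of an unadjusted follow-up score (1):
- Adjusted for week 12: 1 − r², which is 0.75 at r = 0.5 and 0.51 at r = 0.7, so 25% to 49% lower.
- Change from week 12: 2(1 − r), which is 1.00 and 0.60.
- Ratio of change to adjusted: 2(1 − r)/(1 − r²) = 2/(1 + r), which is 1.33 and 1.18.

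**The case against.** The strongest reply is that this is a pilot whose primary endpoint is feasibility, summarised descriptively, and which the article says is not powered for efficacy. The rule therefore touches only exploratory estimates. No bias in the randomised contrast has been shown, and even with no control shift the rule does slightly better than no adjustment (0.269 against 0.276 at r = 0.5). All of this stands and limits the weight of the point. It does not rescue the rule, because the same section commits to inference at 0.05 and to an effect size for each outcome.

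A second reply is that the repeated-measures model already includes week 12 as a time point, so a group-by-time contrast uses each patient's week-12 value. This also stands. The fair comparator for the fix is then change from week 12, and the gain is about 1.2 to 1.3 times. A reader might infer that adjustment is worth twice the sample: 1/(1 − 0.49) = 1.96. That figure holds only against an unadjusted single-time score at r = 0.7.

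A third reply is that the high selection probabilities need large shifts. The named examples are BMI, medication and comorbidities, and controls share the selection criteria except for knee pain and arthroplasty history. A reader might infer that these variables are bound to be flagged. The documents do not support that, nor do they say that pain or function is tested, which is why the full range of shifts is shown.

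Other stronger readings also fail:
- **The covariate set differs by outcome.** The text reads as one set, chosen once.
- **The SD for the definitive trial is spoiled.** The SD of the knee score (KOOS) can be computed from raw data by arm, whatever the covariates.
- **The week-12 value enters only if it tests significant.** Baseline is before surgery, so week 12 is not a candidate under the rule at all.
- **Twenty tests give a 64% chance of a false flag between the two arms.** The figure 1 − 0.95²⁰ = 0.64 applies to independent three-group tests when all three groups are equal, and the protocol fixes neither the number of variables nor a two-arm baseline test.

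**Conclusion.** The concern holds as a flaw in a rule that the protocol states; it is not a complaint about detail left to an analysis plan. The three-group test selects covariates according to patient-versus-control differences and chance. At 26 per group, selection with identical TKA arms runs from 10% to 96% over assumed control shifts of 0.2 to 1.0 SD, while a 0.5 SD imbalance between the arms is caught a third of the time. The size of the precision loss depends on which variables happen to be selected: substantial if a prognostic variable is missed, small if it is picked up. The possible loss of part of the TKA-versus-control gap is conditional on pre-operative pain or function being tested. The shifts and correlations are assumptions. The consequences stay within the exploratory efficacy results and do not reach the feasibility endpoint.

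**What to change.** In the Statistical analysis section:

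1. Delete the baseline significance tests and the covariate rule that depends on them. Report baseline data descriptively by group.
2. For the randomised two-arm comparison at weeks 24 and 52, name the week-12 value of the same outcome as the covariate.
3. Analyse TKA patients against asymptomatic controls separately, with confounders named in advance. Age, sex and BMI are one reasonable example; restricting the list to age and sex is not required. Do not adjust this comparison for pre-operative pain or function.

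The cost is wording and about one degree of freedom in the two-arm model. No new data are needed, because Table 1 schedules the repeated outcomes at week 12 for TKA patients.
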